### Objectives {7}

The purpose of ‘the PIONEER study’ is to conduct a randomized controlled trial in surgically treated patients with DIACFs who undergo rehabilitation with either PWB or Restricted Weight Bearing (RWB). The primary aim of the study is to explore functional outcomes for surgically treated patients with DIACFs and will be allocated to one of the two distinct rehabilitation protocols (PWB or RWB) over a 6-month period. Secondary objectives include comparing disparities in additional functional outcomes and health-related quality of life (HRQoL). Additionally, variances in radiographical parameters (Böhlers angle and posterior facet joint alignment), cost-effectiveness, and complication rates will be assessed and compared.

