#### Secondary outcomes

Secondary outcomes encompass several measures.The Maryland Foot Score (MFS): The MFS is a tool for assessing foot disorders, comprising evaluations of pain, gait, functional activities, and cosmesis. Scores range from 0 to 100 points, with < 50 indicating poor, 50–74 as fair, 75–89 as good, and 90–100 as excellent outcomes [22]. Time points: collected at 2 weeks, 6 weeks, 12 weeks, and 6 months post-surgery.Health-related quality of life (HRQoL) using the EuroQoL 5-Dimension 5-Level (EQ-5D-5L): This self-administered questionnaire comprises five dimensions (mobility, self-care, daily activities, pain/discomfort, and depression/anxiety), each rated on five levels. Utilities calculated using preferences from the Dutch tariff will enable Quality Adjusted Life Years (QALY) scoring, besides the questionnaire is recommended by the Dutch guidelines [23, 24]. Time points: collected at baseline, 2 weeks, 6 weeks, 12 weeks, and 6 months post-surgery.Radiographical characteristics: Evaluation of Böhlers angle and posterior facet joint alignment via radiographic assessment by a blinded radiologist will be conducted at scheduled physician visits. CT scans early post-operatively and at 6 months will be used to measure differences in Böhlers angle and posterior joint alignment [25]. Differences in the Böhlers angle and posterior joint alignment (Δ = CT_6months_—CT_post-op._) will be calculated. Normal Böhlers angle ranges between 25° and 40° [26]. Intra-articular step-off or gap < 2 mm of the posterior facet is considered well-reduced [3]. Time points: early post-operative (‘baseline’) and at 6 months post-surgery CT scan.Medical consumption and productivity: Measured using the Medical Consumption Questionnaire (iMCQ) and Productivity Costs Questionnaire (iPCQ). The iMCQ assess healthcare utilization, while the iPCQ captures productivity losses. The iPCQ and iMCQ are generic and complimentary questionnaires, that can be used in every indication and are adapted to the context of this study [27]. Time points: collected at baseline, 12 weeks, and 6 months post-surgery.Total complication rate: A wound infection is defined as (but not limited to) purulent wound drainage, inflammation, erythema, fever, increased white blood cell count, increased C-reactive protein and/or increased erythrocyte sedimentation rate, necessitating admission for antibiotic treatment and/or revision surgery for infection.A dislocation is defined as the migration of fracture parts, defined as >3 mm articular step-off or gap and/or varus/valgus malalignment > 5° after weight bearing. A non-union is defined as no radiographic union achieved after 6 months or no progress in healing. Failure of osteosynthesis is defined as loosening or breakage of implants, including the rate of reoperation (e.g., leading to removal of material, arthrodesis). Postoperative arthritis will be screened on CT scans. Time points: evaluated at 2 weeks, 6 weeks, 12 weeks, and 6 months post-surgery.

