#### Secondary study parameters

The MFS score at 6 months will be analyzed using a linear regression model to compare between the PWB and RWB groups, similar to the analysis of the primary study parameter. EQ-5D scores at 6 months will be compared between groups using a linear mixed-effects regression model to account for clustering of multiple observations within each patient. Both absolute differences between groups, as well as the difference in slope over time will be estimated. All parameters will be reported, including 95% confidence interval. Binary secondary outcome variables (i.e., having received any secondary surgical procedure, experienced any type of complication, showing differences on radiographs) will be compared between groups using logistic regression analysis.

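### Radiographic change is defined as a continuous CT difference, but the only between-group analysis stated is a logistic regression of a yes/no variable with no threshold or direction

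*Protocol article*

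**What the plan says.** Objectives {7} makes the radiographic comparison a secondary objective: "variances in radiographical parameters (Böhlers angle and posterior facet joint alignment), cost-effectiveness, and complication rates will be assessed and compared".

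Outcomes {12}, Secondary outcomes, defines the measurement. It states that "CT scans early post-operatively and at 6 months will be used to measure differences" in Böhler's angle and posterior joint alignment, read by a blinded radiologist, and then that "Differences in the Böhlers angle and posterior joint alignment (Δ = CT_6months_—CT_post-op._) will be calculated". This is a signed, continuous change for each patient.

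Statistical methods {20a}, Secondary study parameters, gives a linear regression for the Maryland Foot Score and a linear mixed model for EQ-5D. Radiographic change appears only in the last sentence, in the list that opens "Binary secondary outcome variables (i.e., having received any secondary surgical procedure, experienced any type of complication" and ends "showing differences on radiographs) will be compared between groups using logistic regression analysis".

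Three sets of radiographic values appear in the Secondary outcomes section, each for another purpose:
- A reduction-quality criterion: "Intra-articular step-off or gap < 2 mm of the posterior facet is considered well-reduced".
- Part of the definition of dislocation, which is a complication: ">3 mm articular step-off or gap and/or varus/valgus malalignment > 5° after weight bearing".
- A normal range of 25° to 40° for Böhler's angle, which describes the angle itself and not its change.

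**The concern.** The outcome is defined one way and analysed another. The plan commits to calculating a numeric change and then names no comparison between arms that uses it. The variable it does compare cannot be reproduced from the text: nothing says how large a change must be to count, or whether a gain and a loss of reduction count alike. A threshold left open can be chosen after the data have been seen.

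The background explains why this matters. It names fear of secondary displacement as a reason why prolonged restriction has persisted, and it calls the safety of early weight bearing in these patients uncertain. The CT change is the measurement closest to that question. Trial design {8} tests secondary outcomes for superiority, so a non-significant result from an inefficient binary test could be taken as evidence that early loading does not shift the fracture.

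**Working it through.** **Inputs from the protocol article.** 46 evaluable patients per arm, 92 in total, 115 recruited; SD 8.5; margin 5; true difference 0; 80% power (Sample size {14}). Significance level 0.05 (Statistical methods {20a}), taken as two-sided for superiority tests.

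**Inputs assumed.** The CT change is normally distributed with equal SD in both arms. A proportion p of controls is classed as showing a difference. The true shift is d SDs. The documents give none of these, so ranges are shown.

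**Step 1. The plan's own figure.** n per arm = 2 × 8.5² × (1.960 + 0.842)² / 5² = 45.4, rounded up to 46. Then 92 / 0.80 = 115. Both figures reproduce with a one-sided 0.025 test. They concern the AOFAS score; no power is stated for the radiographic outcome.

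**Step 2. Information kept after dichotomising.** For a normal variable cut where a proportion p lies beyond the cut, the information kept is φ(z)² / [p(1 − p)], with z the normal quantile at 1 − p. At p = 0.50 this is 0.3989² / 0.25 = 0.637. At p = 0.20 it is 0.2800² / 0.16 = 0.490.

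| p classed as yes | Kept | Lost |
|---|---|---|
| 50% | 0.637 | 36% |
| 30% | 0.576 | 42% |
| 20% | 0.490 | 51% |
| 10% | 0.342 | 66% |
| 5% | 0.224 | 78% |

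The median cut is the best case. The loss passes one half at p = 20.9% and, by symmetry, at 79.1%.

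**Step 3. Power at 46 per arm.** The shift that a linear comparison detects with 80% power is d = (1.960 + 0.842) × √(2/46) = 0.584 SD. The proportion classed as yes in the other arm is then 1 − Φ(z − 0.584). The power of a two-proportion comparison follows.

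| Controls classed as yes | Other arm | Power, binary | Power, continuous |
|---|---|---|---|
| 50% | 72.0% | 58% | 80% |
| 20% | 39.8% | 55% | 80% |
| 10% | 24.3% | 44% | 80% |

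**Step 4. The same loss as sample size.** For d = 0.5 and 80% power, a continuous analysis needs 63 per arm. The binary analysis needs 102 (p = 50%), 115 (20%), 152 (10%) or 217 (5%).

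The continuous figures are unadjusted; they take no credit for adjusting for the post-operative CT value.

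**The case against.** **The CT model may sit elsewhere.** The analysis sentence speaks of radiographs, whereas the change score comes from CT, and Data management {19} separates CT from X-rays taken as indicated. On that reading the binary item concerns plain films and the CT model is left to an analysis plan not shown. This is weak. The Secondary outcomes section places the CT measures under its radiographical heading and calls their reading radiographic assessment. The analysis section is also not silent: it lists the item among binary variables and names its model.

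**Loss of reduction is caught elsewhere.** This stands in part. Migration that meets the dislocation definition is a complication, and any complication is compared between arms. It is pooled there with infection, non-union and implant failure, and smaller loss of reduction does not enter it.

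**Normality is doubtful for step-off and gap.** This also stands in part. These distances cannot be negative and may be skewed, so the percentages are a guide for those two measures, and the fix has to allow for skewness.

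**Stronger readings that the documents do not support.** A reader might infer that any non-zero change counts, so that measurement error would put almost everyone in the yes group. The protocol does not say this and gives no measurement error; the variable is simply undefined. Power figures that need 90% or more of controls classed as yes therefore have no basis. A reader might also infer that most of the information is lost, but that depends on a proportion the plan does not give. Nor is the CT change clearly the only blinded outcome, since the Discussion applies blinding to radiological evaluations in general.

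**Conclusion.** The point holds. A continuous outcome is defined, its comparison is an objective, and the only comparison stated is a logistic regression of an undefined binary version. Under normality the loss is at least about a third of the information, and more than half only if the cut is met by about 21% or fewer, or 79% or more, of patients. For a 0.58 SD shift, power falls from 80% to between 58% and 44% as the control proportion goes from 50% to 10%. The size rests on assumed normality, proportion and shift; the mismatch and the missing threshold and direction do not. The consequence is inefficient testing of smaller loss of reduction, not a failure to record gross displacement. The outcome is secondary, so 46, 92 and 115 stand. The change should be made, but it does not affect the primary analysis.

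**What to change.** In {20a}, take radiographic change out of the binary list and add: 6-month Böhler's angle, step-off and gap will each be analysed as a continuous outcome by linear regression, adjusted for the post-operative CT value, type of surgery and hospital, and reported as a mean difference with 95% CI. Use a robust or bootstrap interval if the residuals for step-off or gap are skewed. Keep any binary version as supportive only, with its threshold and direction written down before the data are seen and its relation to the dislocation definition made explicit.

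The cost is about one sentence. Both CT scans are already scheduled, and type of surgery and hospital are already in the primary model. No further patients, visits or imaging are needed.

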### Interim analyses {21b}

Not applicable; there will be no interim analysis conducted.

### Methods for additional analyses {20b}

Economic evaluation: a cost-effectiveness analysis (CEA) will be performed to assess whether PWB is value for money. Alongside the trial we will collect individual-level data on intervention costs, healthcare costs, patient and family costs, and productivity costs, using an adapted version of the iMCQ and the iPCQ. Costs will be calculated by multiplying volumes (resource use) with unit costs. For the unit costs, we will use the Dutch costing guidelines [32, 33]. Cost prices will be expressed in euros. If necessary, existing cost prices will be updated to 2024 using the consumer price index [23]. Following the Dutch guidelines, an annual discount rate of 1.5% will be applied for the effects, and future costs will be discounted to their present value by a rate of 4% [23]. The Incremental cost-effectiveness ratio (ICER) will be determined based on incremental costs and effects of PWB versus RWB. The robustness of the ICER will be checked by non-parametric bootstrapping. The bootstrapped cost-effectiveness ratios will be subsequently plotted in a cost-effectiveness plane, in which the vertical line reflects the difference in costs and the horizontal line reflects the difference in effectiveness. The bootstrapped ICERs will also be depicted in a cost-effectiveness acceptability curve showing the probability that permissive weight bearing protocol and AO guidelines is cost-effective using a range of ceiling ratios. Additionally, to demonstrate the robustness of our base-case findings a multi-way sensitivity analysis will be performed. In the sensitivity analysis, uncertain factors of assumptions in the base case analysis will recalculated in order to assess whether the assumptions have influenced the ICER, for example by varying cost prices and volumes between minimum and maximum [34].

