### Trial design {8}

The PIONEER study will be a prospective multicenter RCT conducted in the Netherlands, with parallel groups, allocation ratio 1:1. The primary outcome measure will be evaluated based on the principles of non-inferiority. Secondary outcomes on superiority.

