### Sample size {14}

To our knowledge, there is no literature available that directly compared our primary outcome (AOFAS Score) in PWB versus RWB for surgically treated patients with DIACFs. Therefore, unfortunately, the MCID is unknown for the AOFAS Score [28, 29].

However, the estimated minimal clinical difference (MCID) can be calculated as one half of the standard deviation (0.5 SD) [30]. Preliminary results of a systematic review that is currently performed by our group, found a mean AOFAS Score of 83.7 (SD 8.5) for the RWB group. 0.5 × 8.5 results in a MCID of 4.3, respectively.

Besides, a recent Cochrane review reported a MCID for the AOFAS Score in other foot conditions that range from 2.0 to 7.9 [29]. This results in a mean MCID of (2.0 + 7.9)/2 = 5, respectively.

For this sample size calculation, a MCID of 5 points was assumed, approximating a 0.5 SD of the estimated mean AOFAS score after RWB for surgically treated patients with DIACFs [30].

In order to be able to detect such a difference between the two groups, assuming that an equal number of patients in both groups will be included, with an alpha of 5% and beta of 20% (power 80%), a pooled SD of 8.5 and a true difference of zero points between the RWB and PWB group the sample size should be at least 46 for both groups = 92 in total. Anticipating a 20% drop out a total of 115 patients must be recruited for this study. The sample size calculation was performed with a two-sample mean test for non-inferiority using the TrialSize package within “R.”

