#### Primary study parameter

For the primary research question, the AOFAS Score at 6 months, a continuous outcome, will be utilized. The relative effectiveness of PWB compared to RWB on the AOFAS score will be analyzed using a linear regression model. The model will be adjusted for the type of surgery and hospital. The objective is to assess the non-inferiority of PWB compared to RWB, with a non-inferiority margin set at 5 points. To evaluate non-inferiority, a two-sided hypothesis test will be conducted to determine whether the lower limit of the confidence interval for the estimated treatment effect exceeds the predefined non-inferiority margin. The corresponding p-value for non-inferiority will be calculated using the input from the estimated model. The assumptions for the linear regression model will be evaluated, including linearity, independence of errors, homoscedasticity, and normality of residuals.

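### No baseline adjustment is named for incremental cost: adjusting for pre-injury paid work, on a productivity form already collected at baseline, would remove avoidable noise at almost no cost

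*Protocol article*

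**What the plan says.** All references are to the protocol article.

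- **Methods for additional analyses {20b}.** The data to be gathered are "individual-level data on intervention costs, healthcare costs, patient and family costs, and productivity costs, using an adapted version of the iMCQ and the iPCQ". The estimator is then given as: "The Incremental cost-effectiveness ratio (ICER) will be determined based on incremental costs and effects of PWB versus RWB". The section goes on to non-parametric bootstrapping, a cost-effectiveness plane, an acceptability curve and a multi-way sensitivity analysis, whose example varies prices and volumes. No covariate is named for costs.
- **Secondary outcomes.** For the iMCQ and iPCQ the schedule is: "Time points: collected at baseline, 12 weeks, and 6 months post-surgery".
- **Inclusion criteria.** The age range of 18 to 67 years is labelled as the labor force. Neither the inclusion nor the exclusion criteria ask for paid work.
- **Sequence generation {16a}.** Permuted blocks of random size are described, with no stratification factor.
- **Primary study parameter.** Here covariates are named: the AOFAS model adjusts for type of surgery and hospital.

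**The concern.** People of working age without a job can enrol. If productivity cost means lost paid work, theirs is zero in either arm, while for a worker with a calcaneal fracture it may be a large item. Pre-injury work status is therefore likely to be a strong predictor of 6-month cost, and it is fixed before treatment.

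Permuted blocks balance the numbers per arm but not the share of workers. In a single trial of this size the arms can differ by several percentage points in that share, and an unadjusted cost difference absorbs the gap. The sensitivity analysis given as an example does not address this.

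The section Explanation for the choice of comparators {6b} says costs may be decisive when the two regimens give similar patient-reported results, and the sample size assumes a true AOFAS difference of zero. Precision on the cost side is therefore worth having.

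**Working it through.** **1. The plan's own sample size.** The inputs are "with an alpha of 5% and beta of 20% (power 80%), a pooled SD of 8.5 and a true difference of zero points" and, from Primary study parameter, "with a non-inferiority margin set at 5 points".

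n per arm = 2 × (1.960 + 0.842)² × 8.5² / 5² = 45.4, rounded up to 46, so 92 in total. Then 92 / 0.80 = 115. This matches "the sample size should be at least 46 for both groups = 92 in total" and "Anticipating a 20% drop out a total of 115 patients must be recruited for this study", with one-sided 0.025. One-sided 0.05 would give 36 per arm. With "with parallel groups, allocation ratio 1:1", 115 recruited is 57.5 per arm. The economic evaluation states no figure that could be reproduced.

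**2. Chance imbalance in paid work.** The share in work, p, is an assumption. SD of the difference between arms = √(2p(1−p)/n).

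| p | SD, n = 57.5 | P(gap ≥ 10 points) | SD, n = 46 | P(gap ≥ 10 points) |
|---|---|---|---|---|
| 70% | 8.6 points | 24% | 9.6 points | 30% |
| 80% | 7.5 points | 18% | 8.3 points | 23% |
| 90% | 5.6 points | 7% | 6.3 points | 11% |

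At an assumed mean productivity cost of EUR 10,000 per worker and n = 57.5, this imbalance alone gives the cost difference an SD of EUR 560 to 855. The figure scales in proportion to the assumed cost.

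**3. Share of productivity-cost variance due to work status.** Assumptions: p = 60-90%, mean in workers m = EUR 10,000-15,000, SD in workers s = EUR 6,000-8,000, zero in non-workers.

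Share = p(1−p)m² / [p·s² + p(1−p)m²].

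- Low corner (90%, 10,000, 8,000): 9.0 / (57.6 + 9.0) = 14%.
- High corner (60%, 15,000, 6,000): 54.0 / (21.6 + 54.0) = 71%.
- Middle case (75%, 15,000, 8,000): 42.2 / (48.0 + 42.2) = 47%.

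(The terms are in millions of squared euros.)

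For the middle case with 57 per arm:

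- Unadjusted SE = √(2 × 90.2 million / 57) ≈ EUR 1,780.
- SE adjusted for work status = √(2 × 48.0 million / 57) ≈ EUR 1,300.
- A one-SD imbalance is √(2 × 0.75 × 0.25 / 57) = 8.1 points, which moves the difference by 0.0811 × 15,000 ≈ EUR 1,217.
- A simulation of 5,000 trials with gamma-distributed costs gave SDs of 1,798 and 1,282, in line with the formula.

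**4. Adding the other cost items.** Scale costs to the mean for a worker. Let CV be the coefficient of variation in workers (0.5 to 1.0), p = 70-90%, and k the SD of all other costs, taken as independent of work status.

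Share = p(1−p) / [p(1−p) + p·CV² + k²]; reduction in SE = 1 − √(1 − share).

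| Other costs | Share due to work status | Reduction in SE |
|---|---|---|
| k = 0 (productivity cost only) | 9-55% | 5-33% |
| k = 0.5 | 7-33% | 4-18% |

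The 4-33% range for the SE comes from this table. The corners in step 3, which exclude other costs, would give 1 − √0.86 = 7% and 1 − √0.29 = 46%.

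**The case against.** **The text is silent; it does not state an unadjusted analysis.** A reader might infer that the plan commits to comparing raw costs. It does not say so. The article condenses a longer protocol that is available on request, and cost covariates may be specified there or in an analysis plan. This stands, so the point cannot be called an error. Against it, the economic section is fairly detailed (cost categories, price year, two discount rates, bootstrap, plane, curve), and the AOFAS section names its covariates. That makes it worth stating them for costs too.

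**A reader might infer bias, or that the employment mix determines the ICER.** Neither follows. Randomisation makes the raw difference unbiased, and the bootstrap carries the extra variance into the plane and the curve. Under most of the scenarios in step 4 work status accounts for a minority of the variance. What the bootstrap does not do is remove variance that a baseline covariate could explain.

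**A reader might infer that non-workers should not be pooled with workers.** The mean societal cost difference over everyone enrolled is a legitimate target. Adjustment is a choice made for efficiency.

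**The remedy depends on a form that is not shown.** The article says the questionnaires were adapted and that the iPCQ captures productivity losses. It does not say that pre-injury work and hours are recorded, or that losses are confined to paid work. Patients have a week after surgery to decide on participation, so the baseline form may be completed after injury. This stands and limits which covariates are safe.

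**Conclusion.** The point holds as a near-free improvement in precision. The documents show that non-workers are eligible, that no stratification by work is stated, that a productivity form is collected at baseline, and that no covariate is named for incremental cost. They do not show bias or a contradiction.

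All of the sizes are assumed. Work status would explain about 14-71% of productivity-cost variance in the euro scenarios, and about 7-33% of total-cost variance if other costs have an SD of half the mean worker cost. In the scaled scenarios the SE falls by about 4-33%, and by 4-18% once other costs vary. The low end applies when nearly everyone works and costs vary widely among workers; the high end applies when fewer work and productivity cost dominates. The calculation takes productivity cost as zero in non-workers and other costs as independent of work status. It adjusts for work status only, so any gain from hours is not counted.

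**What to change.** In Methods for additional analyses {20b}, or in the analysis plan if it is not already there:

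- Estimate incremental cost from a regression of 6-month cost on arm, pre-injury paid-work status and pre-injury weekly hours, taken from the baseline iPCQ.
- Refit the model in every bootstrap replicate, so that the ICER, plane and acceptability curve all use the adjusted difference.
- Keep the unadjusted difference as a sensitivity analysis.
- Add baseline iMCQ cost only if that form refers to the period before injury.

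**Cost.** One or two sentences and a few lines of code. No new data are needed, provided the adapted baseline form records pre-injury work and hours; that should be checked first. A few missing baseline values will need imputing.
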